### **2.3.1 Inclusion Criteria**

Adult women, aged over 18 years old, who were diagnosed and treated with GDM during the period 2010 – 2011.

### **2.3.2 Exclusion criteria**

Women with known Type I or T2DM prior to the index pregnancy will be excluded from the study.

For the HbA1c test, women with the following will be excluded from the final analysis:

- Women who are being treated for chronic renal failure or
- Women who are being treated for iron deficiency anaemia or
- Women who are already on treatment for T2DM

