### **1.1.1 Gestational diabetes and prevalence of type 2 diabetes mellitus**

Gestational diabetes mellitus (GDM) is a known risk factor for the development of T2DM (6). Initially GDM was defined as glucose intolerance first presenting in pregnancy with return to normal glucose tolerance post pregnancy (6). More recent definitions include both women with pre-existing diabetes first recognized in pregnancy and women who manifest glucose abnormalities for the first time during pregnancy. There is still no consensus on the mechanisms underlying the development of GDM, although greater insulin resistance in GDM women compared to matched pregnant controls during the third trimester of pregnancy has been reported by several authors (7-9), lending weight to the role played by insulin resistance in the pathophysiology of GDM.

Several studies have demonstrated that the prevalence of GDM varies in different populations (10-12), because this is directly related to the specific population prevalence of T2DM. Recent systematic reviews of the small number of available studies in Africa estimate GDM prevalence to be between 0 and 14% (13). In South Africa, evidence from an ongoing unpublished study (Soweto pilot study) estimates the GDM prevalence to be higher than 15%.

Systematic reviews, primarily based on data from high income countries have reported that women with previous GDM have a seven-fold risk of developing T2DM (6,14), increased risk of long term cardiovascular disease (15,16) and risk of adverse perinatal outcomes for the GDM offspring (15,16). Research from high income countries has also shown that the majority (around 50%) of the women who progress to T2DM after GDM do so within the first 5 years after the GDM pregnancy (17). In addition, the prevalence of T2DM in women with

previous GDM varies widely in different populations, Kim et al, for example, found that T2DM prevalence ranged from a low 3% in some populations to as high as 70% in other populations (17). There is no data on the proportion of women with previous GDM who progress to T2DM and associated risk factors in Sub-Saharan Africa where, unlike the high-income countries, there are high rates of food insecurity and obesity co existing with malnutrition together with a potentially different genotype.

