### **1.2 Aim and Objectives**

The aim of the study is to determine the prevalence of and risk factors for T2DM in women who had GDM 5 years previously, in South Africa.

The aim will be achieved by the following objectives;

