#### **1.3.1 Objectives**

1. To estimate the prevalence of T2DM in women who were diagnosed and received management for GDM 5-6 years previously by using a glucose tolerance test to identify women with T2DM.
2. To investigate the other subsequent factors for the development of T2DM in women who were diagnosed and received management for GDM 5-6 years previously.

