## **2.6 Medical chart review**

Clinical data pertinent to the index pregnancy will be collected via a review of the individual patient hospital records, using a structured data collection form. Data collected will include: maternal age gestational age and OGTT result at time of GDM diagnosis, insulin and oral hypoglycemic agent use during GDM, BMI at booking, infant birthweight (macrosomia or not – using birthweight of 4000g as cut off), and outcome of pregnancy (stillbirth and fetal complications), parity, previous GDM, and comorbidities such as pre-eclampsia, lipid levels if measured and diabetes therapy at time of discharge.

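### Only diabetes known before the index pregnancy is excluded, so prevalence cannot be read as progression and the risk-factor model for Objective 2 mixes diabetes probably present at index with later development

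*Protocol*

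**What the plan says.** Eligibility rests on two short rules. Section 2.3.1 admits adult women "who were diagnosed and treated with GDM during the period 2010 – 2011". Section 2.3.2 then states: "Women with known Type I or T2DM prior to the index pregnancy will be excluded from the study". Neither section refers to the level of the index OGTT or to a test after delivery.

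The background in 1.1.1 describes two ways of defining GDM. The initial one was "glucose intolerance first presenting in pregnancy with return to normal glucose tolerance post pregnancy". Against that, "More recent definitions include both women with pre-existing diabetes first recognized in pregnancy", together with women whose glucose first becomes abnormal in pregnancy. The protocol does not say which definition the hospital register followed or which one the study adopts.

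The aim (1.2 Aim and Objectives) is to "determine the prevalence of and risk factors for T2DM in women who had GDM 5 years previously". Objective 1 in 1.3.1 is a prevalence. Objective 2 is worded differently: "To investigate the other subsequent factors for the development of T2DM in women". The evidence gap named in 1.1.1 is likewise about progression: "There is no data on the proportion of women with previous GDM who progress to T2DM".

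Section 2.6 abstracts the index OGTT result, gestational age at diagnosis, insulin and oral agent use in the pregnancy, and "diabetes therapy at time of discharge". Section 2.13.2 plans a multivariable logistic regression for risk factors, with candidates screened at a univariate p-value below 0.1. It places no restriction on the women who enter the model, and it does not use the index data to separate diabetes already present from diabetes that came later.

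**The concern.** A woman who was already diabetic at the index pregnancy cannot develop diabetes afterwards. If her diabetes had not been recognised, 2.3.2 does not remove her. If she is diabetic at the study visit, she is a case in the risk-factor model alongside women whose diabetes arose later.

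Two readings of the results are then at risk:

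- **Progression.** The background and rationale invite a reader to take the prevalence figure as the proportion who progress. With women already diabetic in both numerator and denominator, it is too high for that purpose.
- **Predictors.** For these women, a high index glucose and use of insulin or discharge therapy may be signs of the diabetes itself. If tested as candidates, such variables could pass the 0.1 screen and show large odds ratios partly because they measure the outcome. Section 1.2 Rationale and Motivation wants the evidence to inform prevention, so the difference between predicting future diabetes and recognising existing diabetes matters.

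**Working it through.** **Inputs from the protocol (2.11 Sample Size).** Hypothesised prevalence p = 0.40, precision d = 0.05, z = 1.96, population N = 498, expected recruitment 50%.

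**Input not in the protocol.** The share f of the cohort already diabetic at index. I assume 2% to 20%. I also assume a proportion r of these women who are diabetic at follow-up and counted as cases: 100% in the main calculation, 80% to 90% as a check.

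**Step 1: the plan's own figure.**
n0 = p(1 − p)z²/d² = 0.24 × 3.8416 / 0.0025 = 368.8.
With the finite-population correction, n0 / (1 + (n0 − 1)/N) = 368.8 / (1 + 367.8/498) = 212.1, rounded up to 213. The stated 213 is reproduced, and this point does not affect it.

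**Step 2: what an observed 40% would mean for progression.**
Observed prevalence = f·r + (1 − f)·q, where q is the proportion diabetic at follow-up among women not diabetic at index. Hence q = (0.40 − f·r)/(1 − f). With r = 1:

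| Assumed f | q | Overstatement (points) | Share of all cases already diabetic at index (f/0.40) |
|---|---|---|---|
| 2% | 0.38/0.98 = 38.8% | 1.2 | 5% |
| 5% | 0.35/0.95 = 36.8% | 3.2 | 12.5% |
| 10% | 0.30/0.90 = 33.3% | 6.7 | 25% |
| 15% | 0.25/0.85 = 29.4% | 10.6 | 37.5% |
| 20% | 0.20/0.80 = 25.0% | 15.0 | 50% |

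**Step 3: where the overstatement equals the planned precision.**
Set q = 0.35: 0.40 − f·r = 0.35 − 0.35f, so f = 0.05/(r − 0.35).
- r = 1: 0.05/0.65 = 7.7%
- r = 0.9: 0.05/0.55 = 9.1%
- r = 0.8: 0.05/0.45 = 11.1%

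**Step 4: effect of r < 1 on the size.**
- f = 10%, r = 0.8: (0.40 − 0.08)/0.90 = 35.6%, overstatement 4.4 points
- f = 15%, r = 0.8: (0.40 − 0.12)/0.85 = 32.9%, overstatement 7.1 points
- f = 20%, r = 0.9: (0.40 − 0.18)/0.80 = 27.5%, overstatement 12.5 points

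**Step 5: what a restricted model would have to work with.**
Expected recruitment is 0.50 × 498 = 249 women, or 249 × 0.40 = 99.6, about 100 cases. With r = 1 and a perfect flag, removing f = 10% leaves about 224 women and 75 cases. Removing f = 20% leaves about 199 women and 50 cases.

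**The case against.** The strongest reply is that the study is a prevalence study. The aim, Objective 1, the design in 2.1 and the sample size in 2.11 all concern cross-sectional prevalence among women treated for GDM. A woman with T2DM at the visit is a correct prevalent case whenever it began. This stands. A reader might infer that the prevalence estimate itself is biased or that 2.3.2 must be tightened, but the documents do not support that. Comparing the shift with the 5-point precision only gives a sense of scale for the progression reading.

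A reader might also infer that the eligibility rule contradicts a GDM definition adopted by the protocol. It does not: 1.1.1 is background, describes two definitions and adopts neither. What remains is that the mix of women is left open.

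Nor is it certain that every such woman would be counted as a case. The main outcome in 2.4 is set by the OGTT, 2.9 excuses women already on treatment for T2DM from it, and their classification is not stated. The arithmetic assumes that they are counted. Untreated women with a diabetic OGTT result would be cases under 2.4.

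The size rests wholly on assumed shares. At 2% or 5% it is below the planned precision, so a claim of a large distortion would go beyond the documents.

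It can also be said that flags and sensitivity analyses belong in an analysis plan that is not shown. That is fair for the detail. However, the protocol itself fixes an eligibility rule and a risk-factor model, and together they do not match the wording of Objective 2.

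Finally, making a restricted model the main one is open to question. It would truncate index glucose and treatment, which may be genuine predictors, and it would lose cases from about 249 women. Nothing in the documents shows that a high index OGTT or discharge therapy proves diabetes before pregnancy. This argues for a sensitivity analysis rather than a replacement of the main model.

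**Conclusion.** The point holds for Objective 2 and for any statement about progression, but not for Objective 1. As written, the plan lets unrecognised pre-existing diabetes into the cohort and analyses it together with diabetes that developed after the index pregnancy, although the protocol's background shows awareness that the GDM label can cover both. Associations of index glucose and treatment with T2DM would therefore be hard to interpret. That difficulty does not depend on the overstatement reaching the planned precision.

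For an observed 40%, the overstatement of progression runs from about 1 point (2% of women) to 15 points (20%) if all of them are still diabetic and counted. It passes 5 points at about 8%, or at about 9% to 11% if only 80% to 90% are. These shares are assumptions, and the documents do not allow the actual size to be established.

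**What to change.** In 2.13.2:

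- Define a flag for probable diabetes at index from the OGTT result at GDM diagnosis and the therapy at discharge, both already abstracted under 2.6. Write down the cut-off before analysis. Put women whose records do not allow a decision in a separate unclassifiable group.
- Report T2DM prevalence overall, as now planned, and by flag group. Say that the overall figure is a prevalence and not a proportion progressing.
- Keep the risk-factor model in all women and prespecify a repeat without flagged women as a sensitivity analysis for Objective 2. State how the unclassifiable group is handled in it.
- State how women already on treatment for T2DM are classified for the outcome, since both the split and the model depend on it.

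The cost is a few sentences, with no new visits or samples. The restricted model will have fewer women and cases, and the flag will misclassify some women in both directions, so the two models should be reported side by side.

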## **2.4 Measurements**

Diabetes as defined by the result of the 75g 2hour OGTT, as defined according to the WHO 2006 guidelines will be the main outcome. Other outcomes will include impaired fasting glucose and impaired glucose tolerance.

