## **2.9 Oral Glucose Tolerance Test and HbA1c**

Participants will be given 75g anhydrous glucose in 250ml of water, in the morning after a 10-12 hour overnight fasting period (3). Venous blood samples will be taken at 0 minutes for glucose, lipogram and for HbA1c measurement, at 30 minutes and 120 minutes for glucose

and insulin. The bloods will be kept on ice, and sent to the laboratory for handling and measurement of the same day using commercially available test kits. T2DM will be diagnosed according to WHO guidelines (3). One additional blood sample (5ml each) will be taken from each participant, centrifuged and the serum stored in case some samples get spoiled or if confirmation is needed or an additional investigation relating to GDM is considered. The samples will be stored up to 5 years after the study and thereafter destroyed. Ethics approval will be sought if any additional investigations are performed. Any participants who are already on treatment for T2DM will not be required to do either the OGTT or the HbA1c.

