## **2.11 Sample Size**

Sample size for evaluating the prevalence of postnatal T2DM was calculated using the formula

$$\frac{p(1-p)z^2}{d^2}$$

With  $p$  = the hypothesized proportion of GDM women who have postnatal T2DM,  $z = 1.96$  (corresponding to a 0.05 level of significance) and  $d$  = the precision to which the prevalence is to be estimated.

Most studies found a prevalence of T2DM during the first 5 years after GDM diagnosis between 20% and 50% (14).

The total number of women treated for GDM at the hospital during the period 1 September 2010 to 31 August 2011 was 498. Using 498 as the total population, a hypothesized prevalence of 40% and aiming to estimate the prevalence of T2DM to within 5 percentage points ( $d = 0.05$ ), the study would require a sample size of 213.

Since the population is finite, we will endeavor to recruit all the 498 women, however, conservatively estimate that the study will be able to recruit 50% of these women, as our population is highly mobile and, apart from loss to follow-up and relocation, contact details in the hospital registers are not very accurate and some change their contact details.

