### **2.13.2 Statistical data analysis**

All statistical analysis will be carried out using Stata 14 (37). For all analysis, the level of significance will be set at 0.05, 2-sided p-values and 95% Confidence Interval (95% CIs) will be reported. Crude T2DM prevalence will be calculated taking into consideration the sample design and the realized sample (4). For categorical variables frequencies and proportions will be reported, while bar graphs and pie chart will be used to present data where appropriate. The chi squared test, Fischer's Exact (small frequencies) and McNemar's chi squared Test (paired data) will be used to compare categories.

All continuous data will be tested for Normality using the Shapiro Wilks test and histogram plots. Means and standard deviations will be presented for variables that are normally distributed while medians and IQRs will be reported for variables that do not follow the Normal Distribution. Box and whisker plots, histograms, scatter plots and line graphs will be used to present data where appropriate. The t-tests and ANOVA (more than two groups) will be used to test to compare continuous outcomes between groups if data are normally distributed. For data that are not normally distributed, comparisons will be tested using Mann U Whitney, Wilcoxon sum rank (2 independent groups), Wilcoxon rank tests (paired data) as well as the Kruskal-Wallis for more than two groups.

Multivariate logistic regression, will be used to evaluate risk factors. Odds Ratios (ORs), their 95% CIs and p-values will be reported. Variables with p-values below 0.1 in the univariate analysis will be considered for the multivariate logistic regression. Additional analysis will include subgroup analysis for different ethnicities, should ethnicity prove to be an independent predictor of risk of T2DM.

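### The main outcome rests on the OGTT alone, but eligible women already treated for T2DM need not be tested and no rule counts them as cases; read literally, prevalence is biased downward

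*Protocol*

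**What the plan says.** - **Outcome.** Protocol section 2.4: "Diabetes as defined by the result of the 75g 2hour OGTT, as defined according to the WHO 2006 guidelines will be the main outcome". Objective 1 in section 1.3.1 matches it: prevalence is to be estimated "by using a glucose tolerance test to identify women with T2DM".
- **Eligibility.** Section 2.3.2: "Women with known Type I or T2DM prior to the index pregnancy will be excluded from the study". Only diabetes known before that pregnancy excludes, so a woman who developed T2DM afterwards and is now treated may take part.
- **Testing.** Section 2.9: "Any participants who are already on treatment for T2DM will not be required to do either the OGTT or the HbA1c".
- **Analysis exclusion.** Section 2.3.2 lists women on T2DM treatment under the lead-in "For the HbA1c test, women with the following will be excluded from the final analysis".
- **Prevalence analysis.** Section 2.13.2: "Crude T2DM prevalence will be calculated taking into consideration the sample design and the realized sample". It gives no numerator or denominator rule for treated, untested women.
- **Relevant data.** The questionnaire (section 2.7) records current medications, comorbidities and self-reported postnatal diabetes follow-up. The chart review (section 2.6) concerns the index pregnancy.

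**The concern.** The aim is the prevalence of T2DM, and its risk factors, in women who had GDM five years before. It is not the prevalence of undiagnosed T2DM. A woman diagnosed and treated since the index pregnancy belongs to that target as a case. Under the written rules she is an eligible participant with no value on the only variable that defines the outcome.

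An analyst who follows the text has two choices: leave her out, or let the absence of a positive OGTT make her a non-case. Both push the estimate down, and recruiting more women does not cure it. The logistic regression uses the same outcome, so it would either omit known cases or place them in the comparison group.

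**Working it through.** **Inputs from the protocol (section 2.11).** "a hypothesized prevalence of 40"% for p; precision d = 0.05; z = 1.96; population N = 498. For the range of p: "Most studies found a prevalence of T2DM during the first 5 years after GDM diagnosis between 20% and 50"%.

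**Input not in the protocol.** f, the share of true T2DM cases already on treatment. It is assumed here, from 10% to 75%.

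**Step 1: reproduce the planned sample size.**
- n0 = p(1 − p)z²/d² = 0.4 × 0.6 × 1.96² / 0.05² = 368.8
- With finite population correction: n = 368.8 / (1 + 367.8/498) = 212.1, rounded up to 213

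The stated 213 is reproduced, so the sample size is not in question.

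**Step 2: apparent prevalence under the OGTT-only rule.** Treated cases are a fraction pf of participants.
- Treated women dropped from numerator and denominator: (p − pf)/(1 − pf)
- Treated women kept as non-cases: p(1 − f)

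At p = 40%:

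| f (assumed) | Dropped | Bias, points | Non-cases | Bias, points |
|---|---|---|---|---|
| 10% | 0.36/0.96 = 37.5% | −2.5 | 36.0% | −4.0 |
| 25% | 0.30/0.90 = 33.3% | −6.7 | 30.0% | −10.0 |
| 50% | 0.20/0.80 = 25.0% | −15.0 | 20.0% | −20.0 |
| 75% | 0.10/0.70 = 14.3% | −25.7 | 10.0% | −30.0 |

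**Step 3: when does the bias exceed 5 points at p = 40%?** Let t = pf.
- Dropped: (0.40 − t)/(1 − t) = 0.35 gives t = 0.05/0.65 = 7.7% of participants, and f = 0.077/0.40 = 19% of true cases.
- Non-cases: t = 5% of participants, and f = 0.05/0.40 = 12.5% of true cases.

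**Step 4: vary p from 20% to 50%.**
- f = 10%: bias −1.6 to −2.6 points (dropped), −2.0 to −5.0 (non-cases)
- f = 25%: −4.2 to −7.1, and −5.0 to −12.5
- f = 50%: −8.9 to −16.7, and −10.0 to −25.0
- f = 75%: −14.1 to −30.0, and −15.0 to −37.5

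The sign is negative in every cell; the size depends on f.

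**Step 5: does dropping treated women leave too few for the planned precision?** Expected recruitment is 50% of 498 = 249.
- f = 25%: 249 × 0.90 = 224 remain, above 213.
- f = 50%: 249 × 0.80 = 199 remain. The figure of 213 belongs to p = 40%, whereas apparent prevalence here is 25%. The protocol's formula then gives n0 = 0.25 × 0.75 × 1.96² / 0.05² = 288.1, and n = 288.1/(1 + 287.1/498) = 182.7, or 183 rounded up. So 199 is enough.

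The problem is bias, not loss of precision.

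**The case against.** The best reply is that the test is waived because the woman's status is already known, and that the investigators mean to count her as a case. The text gives this some support. Section 2.9 calls these women participants, the aim refers to T2DM without qualification, and section 2.13.2 speaks of T2DM prevalence, not OGTT-detected prevalence. If that is the intention, the bias disappears. But the rule is not written, and both places that say how T2DM is identified name only the glucose tolerance test. Nor is this a detail that can simply wait for an analysis plan: the protocol has already fixed an outcome definition and a testing waiver that do not fit together.

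Three stronger readings are tempting, and the protocol supports none of them.
- *The protocol removes treated women from the prevalence analysis.* A reader might infer this from section 2.3.2, but that exclusion is limited to the HbA1c test. The loss follows from the OGTT-only definition combined with the waiver.
- *Losing treated women takes the study below its required 213.* Step 5 of the working shows otherwise.
- *Risk-factor associations would be weakened because treated women are the most severe progressors.* This is conceivable, but nothing in the protocol shows that they are more severe or which way each odds ratio would move.

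It is also fair to object that the size is unknown. At p = 40% with 10% of cases treated, the bias is 2.5 to 4 points, inside the planned precision.

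**Conclusion.** The point holds as a defect in the case definition. Taken literally, the main outcome leaves eligible women with known, treated T2DM without an outcome value, and the prevalence estimate is too low under either way of handling them. Only the direction is certain, and only on the literal reading. The size rests on the treated share of cases, which the protocol does not give. At the planning prevalence of 40% the bias runs from 2.5 points (10% treated, dropped) to 20 points (50% treated, counted as non-cases). It exceeds the 5-point target once about one case in five (dropped) or one in eight (non-cases) is treated. For the regression, what can be said is that known cases would be omitted or misclassified. Because this concerns the study's primary estimate and is repaired by wording, it should be settled before analysis.

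**What to change.** - In sections 1.3.1, 2.4 and 2.13.2, define the main outcome as diabetes diagnosed by the OGTT, or T2DM currently on treatment in a woman without known diabetes before the index pregnancy. Identify treatment from the medication and medical-history items in section 2.7.
- State that these women stay in the numerator, the denominator and the logistic regression.
- Report known (treated) and newly detected diabetes as separate components of the total.
- Add a sensitivity analysis restricted to OGTT-tested women.

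The testing waiver in section 2.9 can stay as it is; no extra test is needed and the sample size of 213 stands. The cost is a wording change and some reliance on self-report: the chart review in section 2.6 covers the index pregnancy, and no listed item records the date of a later diagnosis. Confirming a later diagnosis from records would need additional data collection.

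This wording does not cover untreated women seen at community centers, for whom section 2.3 replaces the OGTT with fasting glucose and HbA1c. Their outcome rule has to be reconciled with section 2.4 separately.
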